## Abstract

**Background:**

Obesity and being overweight are major contributing factors for many diseases. Calorie restricted diets often fail to result in sustained long-term weight loss. Very low–carbohydrate, high-fat ketogenic diets have been suggested to have superior metabolic and weight loss effects. Keyto is a low-cost, highly scalable mobile health (mHealth) app paired with a noninvasive biofeedback tool aimed at facilitating weight loss through a personalized healthy and predominantly plant- and fish-based ketogenic diet.

**Objective:**

This protocol describes a randomized trial comparing the efficacy of the Keyto mHealth app and device intervention to that of Weight Watchers’ WW app in individuals who are overweight or obese. The primary outcome is weight loss after 12 weeks. Secondary and exploratory outcomes, including metabolic and cardiovascular risk factors, will be assessed at 12, 24, and 48 weeks.

**Methods:**

A total of 144 participants will be recruited and randomized to either the Keyto program or Weight Watchers program. Study participants will be guided through the study via video conference or phone calls and will undergo a fasting blood analysis performed by a third-party diagnostic lab at weeks 0 and 12 to assess metabolic and cardiovascular risk markers. All participants will be asked to weigh themselves daily on a study-provided Bluetooth-enabled scale. Participants randomized to the Keyto arm will also be asked to measure their breath acetone levels, a measure of ketosis, with the Keyto device 3 times per day.

**Results:**

Recruitment started in December 2019. Rolling recruitment is expected to be completed by July 2020. Data collection and analysis of the primary intervention phase is expected to be completed in October 2020. The 24- and 48-week follow-ups are expected to be completed in January 2021 and July 2021, respectively.

**Conclusions:**

This trial will provide high-quality evidence regarding the efficacy of the Keyto weight loss program in individuals who are overweight and obese in a free-living condition. This study also fills a gap by examining the impact of a ketogenic diet emphasizing plant- and fish-based fats on blood lipid profile and cardiovascular disease risk.

**Trial Registration:**

ClinicalTrials.gov NCT04165707; https://clinicaltrials.gov/ct2/show/NCT04165707.

**International Registered Report Identifier (IRRID):**

DERR1-10.2196/19053

## Introduction

Obesity is a major risk factor for a variety of diseases, including type 2 diabetes, cardiovascular diseases, musculoskeletal disorders, and some cancers [1]. It is estimated that over 40% of adults worldwide attempt weight loss diets each year [2]. Unfortunately, conventional calorie restriction diets often fail to produce long-term weight loss [3]. Therefore, novel dieting techniques must be explored in order to successfully treat obesity and lower disease risk.

Although many different dietary approaches can lead to weight loss [4], increasing evidence suggests that a very low–carbohydrate ketogenic diet may have superior metabolic and weight loss effects [5-10]. On a ketogenic diet, when carbohydrate intake is kept very low (<50 g/day), high rates of lipolysis increase delivery of free fatty acids to the liver, which converts them into ketone bodies (β-hydroxybutyrate, acetoacetate, and acetone) that the brain and body can use as an alternative fuel source. Accumulating evidence suggests that ketones mediate reduced feelings of hunger when individuals follow a ketogenic diet [11,12], which could help facilitate sustained weight loss. A ketogenic or low-carbohydrate diet may also be beneficial because it can potentially increase energy expenditure during weight loss maintenance [13]. When compared to other dietary approaches, the ketogenic diet also provides a unique opportunity to follow and track a biomarker in the form of ketone levels that may provide useful and actionable information.

The effectiveness of any diet is limited by an individual’s ability to adhere. Adherence to a diet requires considerable cognitive and self-regulatory resources daily at every meal or eating opportunity. Meta-analytic evidence suggests that self-regulatory behavior change strategies, such as self-monitoring, play a crucial role in increasing adherence to diet and healthy behaviors [14,15]. Very low-carbohydrate ketogenic diets can be particularly challenging to adhere to because of the complexity of understanding the carbohydrate content of consumed food and whether consuming certain foods will promote or limit ketosis [16,17]. However, the current approaches to self-monitoring ketogenic diets (eg, through finger stick blood monitors, urine ketone strips, or food logs) are typically expensive, painful, inconvenient, or inaccurate. There is emerging technology that can lower the burden of self-monitoring by measuring breath acetone to provide individuals embarking on a ketogenic diet with immediate ketone-specific self-monitoring that could help optimize adherence and success [18].

Keyto (Keyto Inc) is a scalable comprehensive weight loss program that combines resources (eg, recipes, searchable database, menus, meal plans, social support) delivered from a mobile health (mHealth) app with information from an accompanying breath acetone sensor to help individuals learn about and monitor whether they are in ketosis. Because a ketogenic diet is very low in carbohydrates but high in fat, there is some concern as to the impacts of such a predominantly high- (saturated) fat diet on cardiovascular health [19]. Keyto helps to guide users toward more heart-healthy plant- and fish-based fat sources to achieve ketosis. Thus, the goal of the Keyto program is to facilitate weight loss through a personalized healthy and ketogenic diet. As of January 2020, Keyto has delivered over 30,000 Keyto breath acetone analyzers to customers with reported anecdotal success, but robust evidence is required to evaluate the efficacy of this low-cost, scalable weight loss intervention. The purpose of this research is to conduct a pragmatic randomized trial to test the efficacy of the Keyto biofeedback and app intervention compared to Weight Watchers’ WW (Weight Watchers International Inc) diet app. The WW app was chosen as the active comparator as it is a widely accepted dietary approach with robust evidence for its effects on weight loss and cardiovascular health [20]. The hypotheses and exploratory research questions can be found in Table 1.

**Table 1 table1:** Overview of study hypotheses and research questions.

Measures		Outcomes	Timeframe	Hypothesis or question
**Primary outcome**				
	Bodyweight scale	Change in body mass (in kilograms)	12 weeks	Those in the Keyto intervention arm will achieve greater weight loss at 12 weeks than those in the Weight Watchers arm.
**Secondary outcome**				
	Bodyweight scale			
		Change in body mass (in kilograms)	24 and 48 weeks	Those in the Keyto intervention arm will achieve greater weight loss at 24 and 48 weeks than those in the Weight Watchers arm.
		Change in body mass (in kilograms)	Daily weight measured during the first 12 weeks	What are the patterns of body mass change during the first 12 weeks between the 2 study groups?
	Automated self-administered 24-hour dietary recall			
		Carbohydrate intake in 24-hour period (in grams)	12, 24, and 48 weeks	Those in the Keyto intervention arm will report lower carbohydrate intake at 12, 24, and 48 weeks.
		Total fat, saturated fat, polyunsaturated fat, monounsaturated fat intake in 24-hour period (in grams)	12, 24, and 48 weeks	Does the Keyto intervention or WW app intervention influence fat intake from baseline to 12, 24, and 48 weeks?
		Total energy intake in 24-hour period (in kilocalories)	12, 24, and 48 weeks	We will examine changes from baseline to 12, 24, and 48 weeks in total energy intake in the Keyto and Weight Watchers groups.
	Venous blood sample	HbA_1_c^a^, fasting glucose, fasting insulin, fasting high-sensitivity C-reactive protein, fasting HOMA-IR^b^, fasting total cholesterol, fasting HDL^c^ cholesterol, fasting lipoprotein fractions, fasting lipoprotein (a), fasting triglycerides, fasting non-HDL cholesterol	12 and 48 weeks	We will examine changes from baseline to 12 and 48 weeks in metabolic and cardiovascular risk blood biomarkers in the Keyto and Weight Watchers groups.
**Exploratory outcome**				
	Venous blood sample	Fasting albumin, fasting globulin, fasting total bilirubin, fasting alkaline phosphatase, fasting aspartate aminotransferase, fasting alanine aminotransferase	12 and 48 weeks	We will explore changes from baseline to 12 and 48 weeks in blood biochemistry in the Keyto and Weight Watchers group.
**Manipulation checks**				
	Questionnaires			
		Food attitude survey	12, 24, and 48 weeks	We will examine all baseline questionnaires as potential covariates. We will also examine differences in questionnaire measures between the 2 groups at 12, 24, and 48 weeks.
		Cravings, mood, and energy	Weekly	
		Self-reported dietary adherence	Weekly	
		Pittsburgh Sleep Quality Index	12, 24, and 48 weeks	

^a^HbA_1_c: hemoglobin A_1_c.

^b^HOMA-IR: homeostasis model assessment of insulin resistance.

^c^HDL: high-density lipoprotein.

## Methods

### Overview of Protocol

This study is a 2-arm pragmatic randomized clinical trial. Participants will be randomized to one of 2 weight loss conditions: Keyto or Weight Watchers. The primary endpoint will be weight loss at 12 weeks. There will be key secondary endpoints measured at 12 weeks, and weight loss will also be measured at 24 and 48 weeks. Participants will be asked to use the intervention materials for the arm to which they were randomized in their weight loss efforts (ie, Keyto self-monitoring device and app or WW app [21]) throughout the 12-, 24-, and 48-week durations of the primary and secondary phases of this trial. The study has been approved by the corresponding author’s university clinical research ethics board. External peer-reviewed funding was secured from Mitacs, a not-for-profit agency that facilitates academic research collaboration with industry partners.

### Participants and Eligibility

We will recruit 144 adults living in the state of California to participate in the study. Please see Table 2 for a list of eligibility criteria. Because of the coronavirus disease 2019 (COVID-19) pandemic, we have also included COVID-19-specific eligibility criteria in Table 2, which were informed by World Health Organization classifications for symptom severity [22]. Eligibility criteria were established to control for extraneous factors and to maintain a relatively homogeneous sample in this trial. For example, participation was constrained to adults who are overweight or obese and without comorbidities to control for potential differential metabolic impacts of a ketogenic on older adults (who would be more likely to have comorbidities or medications) or those with class 3 obesity [23] who might have more complex conditions.

### Recruitment, Screening, Randomization, Enrollment

Participants will be recruited through Facebook advertisements, poster advertisements placed in public spaces (eg, universities, libraries, coffee shops), and emails to the existing Keyto email list. Informed consent will be obtained digitally via Qualtrics (Qualtrics LLC). Following informed consent, participants will schedule a video conference or phone call with a member of the study team who will answer any questions participants may have, clarify the procedures of the study, and schedule a baseline blood test. After collection of the baseline blood sample, participants will be emailed the online baseline questionnaire. Participants will then be randomized by a researcher logging into a password-protected study website and mailed the study materials for their condition. All 144 participants will be randomized at 1:1 ratio to the Keyto (n=72) or Weight Watchers (n=72) trial arms using a variable permuted block sizes, stratifying for sex (male, female) and age (18-40 years, 41-64 years). The randomization website and schedule will be created and maintained by a third party (Centre for Health Evaluation and Outcomes Science, St. Paul’s Hospital, Vancouver, Canada). Participants will be provided with a US $100 gift card to an online store of their choice upon completion of the 48-week follow-up surveys.

**Table 2 table2:** Trial inclusion and exclusion criteria.

Criteria		
**Inclusion**		
	Aged 18-64 years	
	Living in the state of California	
	BMI 27-43 kg/m^2^	
	Must speak, read, and comprehend English	
	Must have a valid email address and phone number	
	Willingness to a follow an evidence-based very low carbohydrate diet or calorie-restricted diet that have been demonstrated for weight loss	
	Must have a kitchen and be willing to cook	
	Willingness to reduce (net) carbohydrate intake to less than 30 g/day	
	Willingness to restrict intake of added sugar, bread, grain, rice, pasta, sweets, most fruits, pastries, and other carbohydrates	
	Willingness to comply with a strict diet for 12 months	
	Interest in losing weight	
	**(COVID-19^a^ specific criteria) If you have been diagnosed with COVID-19, you may be eligible if:**	
		Do not currently have COVID-19 related symptoms
		Your last symptoms were more than 4 weeks ago
		You experienced uncomplicated or mild COVID-19 symptoms
		You were not hospitalized because of your symptoms
**Exclusion**		
	HIV or immunocompromised	
	Current or past cancer diagnosis	
	Pregnant, breastfeeding, or planned pregnancy in next 12 months	
	Beginning or ending hormonal contraception in next 12 months	
	Current diagnosis of diabetes	
	History of heart attack or stent	
	Currently taking glucose-lowering drugs, statins, or oral steroids	
	History of gastric bypass surgery or any other weight-loss surgery	
	History of anorexia or bulimia	
	History of mental illness	
	Current smoker or smoked cigarettes within past 12 months	
	Currently eating fewer than 50 g carbohydrates per day	
	Currently following ketogenic diet or have strictly adhered to a ketogenic diet for greater than 3 weeks in the past 6 months	
	Lost or gained more than 5% body weight in past 6 months	
	Currently using Weight Watchers or have strictly adhered to the WW app for greater than 3 weeks in the past 6 months	

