### Sample Size Calculation

There are no known studies with protocol design as we describe. Thus, the amount of weight loss expected with a hands-off self-monitoring ketogenic mHealth application is not known. Thus, we determined sample size in order to detect a clinically meaningful 5% difference in weight loss, assuming a mean body mass of 100 kg with a standard deviation of 15 kg [32]. A 5% weight loss corresponds to a small-to-moderate effect size (Cohen *d*=0.33, *f*=0.165). Using G*Power software (version 3.1.9.3) a total sample size of 124 is required to detect a between groups effect with 80% power and α=.05 with 2 groups and 2 time points (primary outcome at 12 weeks) assuming a correlation among repeated measures of *r*=0.75. In order to preserve power and account for 15% loss to follow-up, we will aim to recruit 144 participants (ie, n=72 per group).

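### Table 2 screens out current users of the WW app by product, but screens the Keyto side only by diet, so Keyto owners and occasional users can be randomised to WW

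*Protocol article*

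**What the plan says.** The exclusion list in Table 2 treats the two products differently.

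- Comparator, screened by product: "Currently using Weight Watchers or have strictly adhered to the WW app for greater than 3 weeks in the past 6 months".
- Experimental side, screened by diet: "Currently following ketogenic diet or have strictly adhered to a ketogenic diet for greater than 3 weeks in the past 6 months", together with "Currently eating fewer than 50 g carbohydrates per day".
- Both sides: "Lost or gained more than 5% body weight in past 6 months".

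No line mentions the Keyto app, the sensor or Keyto customers. Under Recruitment, Screening, Randomization, Enrollment, one of the three channels is "emails to the existing Keyto email list"; no corresponding WW channel is listed. The Introduction reports that by January 2020 "Keyto has delivered over 30,000 Keyto breath acetone analyzers to customers". Allocation is 1:1, 72 per arm, stratified by sex and age group only, and Planned Analysis specifies intention-to-treat.

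**The concern.** The first half of the WW rule catches any current user, however casual. The Keyto side has no such clause. A person with a Keyto sensor in a drawer, or who opens the app occasionally while eating normally, passes every criterion, and one recruitment channel reaches out to people with a link to the product. If allocated to WW, that person still holds the experimental tool.

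This matters because the sensor and app are the intervention under test. The Discussion says that the result would support breath ketone monitoring as an adjunct to ketogenic diets. WW participants who use the tool are still analysed as WW, which pulls the 12-week difference in body mass towards zero and costs power against the trial's own primary hypothesis.

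**Working it through.** **Who passes the criteria**

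| Person at screening | WW side | Keyto side |
|---|---|---|
| Current user, following the diet | excluded | excluded (diet rule, and the carbohydrate rule if intake is under 50 g/day) |
| Current user, not following the diet | excluded | eligible |
| Owns the product or account, not using it | eligible | eligible |
| Strictly adherent for over 3 weeks in the past 6 months | excluded | excluded |
| Stopped within 3 weeks, or more than 6 months ago | eligible | eligible |

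Only the second row differs by criterion. The third row is formally alike, but the Keyto email list makes ownership more likely on that side.

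**Reproducing the planned sample size.** Sample Size Calculation aims at a "clinically meaningful 5% difference in weight loss, assuming a mean body mass of 100 kg with a standard deviation of 15 kg", so the difference is 5 kg, with correlation 0.75, α = 0.05 (taken as two-sided) and 80% power.

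- Baseline-adjusted SD: 15 × √(1 − 0.75²) = 9.92 kg.
- n per arm = 2 × (1.960 + 0.842)² × 9.92² / 5² = 61.8, so 62 per arm and 124 in total. This is the stated 124.
- For 15% loss, 124 / 0.85 = 146, close to the stated 144.

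The article does not name this method. It is the one variant tried that gives 124, and it serves here only as a working basis for power.

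**What leakage would cost.** Let c be the fraction of the Keyto effect that reaches the WW arm on average:

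c = (share owning) × (share of owners who use it) × (share of the effect they obtain).

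The article gives none of the three, so every value of c is an assumption. The intention-to-treat difference is 5 × (1 − c) kg. The standard error with 62 per arm is 9.92 × √(2/62) = 1.782 kg, and power = Φ(difference / 1.782 − 1.960).

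| c (assumed) | Difference, kg | Power | Total N for 80% power, before loss |
|---|---|---|---|
| 0 | 5.0 | 0.80 | 124 |
| 2.5% | 4.875 | 0.78 | not computed |
| 5% | 4.75 | 0.76 | 138 |
| 10% | 4.5 | 0.71 | 154 |
| 20% | 4.0 | 0.61 | 194 |

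The 2.5% row corresponds, for example, to 20% owners × 25% of them using it × 50% of the effect; its power is Φ(4.875/1.782 − 1.960) = Φ(0.776) = 0.78. The 5%, 10% and 20% rows correspond to 3.6, 7.2 and 14.4 of 72 WW participants obtaining the full effect. That is pessimistic, since eligible owners are people not following the diet at entry.

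**The case against.** The strongest reply is that the gap is narrow. The ketogenic-diet rule has the same 3-week and 6-month limits as the WW rule and is wider in one respect, because it covers any ketogenic diet and not only Keyto's. Since Keyto is a ketogenic program, its active, adherent users are already out. Being on an email list is not owning a sensor, and owning one is not using it. Leakage would also work against the trial's hypothesis; it would not create a false Keyto benefit. All of this stands, and it limits the point to owners and non-adherent users.

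Three stronger readings are tempting, and the article does not support them.

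- **Carry-over from lapsed Keyto customers as a one-sided flaw.** Lapsed WW users enter on the same terms. Past exposure precedes randomisation and is balanced between arms in expectation. The email list may tilt the sample towards former Keyto users, but that bears on who the result applies to, and its direction is unclear.
- **Contamination as undetectable.** Dietary recall measures carbohydrate intake in both arms at baseline and at 12, 24 and 48 weeks, so a WW participant eating ketogenically might show up. In App Data, only breath acetone is limited to the Keyto group. These measures can hint at leakage but cannot identify use of a privately owned sensor or account.
- **Ownership as unrecorded.** The article does not list it among baseline characteristics, but screening forms commonly sit in the full protocol. It cannot be said that nobody asks.

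It is also fair to say that a WW participant could buy the sensor and download the app after randomisation. An entry criterion cannot prevent that, which is why the remedy needs a follow-up question as well.

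**Conclusion.** The point holds in limited form. The criteria exclude current use of the comparator product but not current use of the experimental product, and one recruitment channel draws on people linked to the experimental product. The diet exclusions leave a residual group of owners and intermittent users who are not on the diet. Some may be randomised to WW with the tool in hand.

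The direction of any effect on the primary comparison is dilution. Its size cannot be determined: the 4.875 to 4.0 kg range, with power of 0.78 to 0.61, rests on assumed values of c, on the 5 kg design difference and on the baseline-adjusted reading of the sample size. A small loss is more plausible than a large one, given who remains eligible. The gap does not undermine the randomisation or invalidate the comparison. It is worth closing because it is avoidable and cheap to close.

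**What to change.** 1. Add to Table 2 an exclusion built like the WW rule: currently using the Keyto app or device, or having used it for more than 3 weeks in the past 6 months. It should rest on use, as the WW rule does; excluding everyone who merely owns a sensor would go further than that rule.
2. At screening, record ownership and past use of either product, unless the full protocol already does so. Ask those already enrolled retrospectively, with identical wording in both arms, because their answers come after allocation.
3. At 12 weeks, ask WW participants whether they used the Keyto app or a sensor. Report the answers descriptively. This is behaviour after randomisation and should not decide who enters the primary analysis.
4. Repeat the primary comparison without participants in either arm who owned or used Keyto before entry, as a sensitivity analysis. The intention-to-treat analysis stays primary.

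The cost is one eligibility line, a few questions and one extra analysis. The pool from the Keyto list becomes slightly smaller, although subscribers who do not use the product remain eligible. The Results section reports 49 enrolled as of April 2020, so from that date the exclusion could apply only to the remaining 144 − 49 = 95; for those already enrolled, only the retrospective question and the sensitivity analysis help.

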	**(COVID-19 specific criteria) If you have been diagnosed with COVID-19, you may be ineligible if:**	
		You have had moderate to severe COVID-19 associated disease
		You have been hospitalized by COVID-19

^a^COVID-19: coronavirus 2019 disease.

### Interventions

#### Keyto App and Device

Those randomized to the Keyto arm will be asked to download the Keyto app from an app store. They will receive a unique email username and password provided by the study team to log in. Participants will be guided through connecting their iHealth scale and the Keyto app and given a brief overview of its features, with the remainder of the intervention will be delivered entirely via the app. The app contains resource information about what to eat and what not to eat in order to achieve nutritional ketosis and ample resources. The app also contains a social support function. For the trial, all Keyto participants will be placed into a moderated support group of 4 to 6 participants per group. Keyto’s registered dietician and executive medical director will be added to each group to answer questions about Keyto and starting a ketogenic diet. The identities of each user will be kept anonymous and users will be encouraged to refrain from using their names in this forum. Based on the premium version of the Keyto app, a phone or video conference call with the registered dietician will be available in the second week of the program. The app also includes tips and resources about how to succeed potential side effects or pitfalls. There is access to a short podcast offered 3 times per week discussing various aspects of the program including strategies and pitfalls.

The Keyto app uses its Key Eats nutrition plan as a heart-healthy ketogenic diet that emphasizes fish and plant-based fats, moderate protein and nonstarchy vegetables and is compatible with a vegetarian or mixed-diet lifestyle. The app reinforces users to avoid foods with refined carbohydrates like pasta, bread, pizza, or sweets and replacing those with foods high in healthy fats such as avocados, nuts, fatty fish (such as salmon), and olive oil.

The Key Eats Code is a searchable database of almost all foods that rates each using a red, yellow, or green code to indicate whether to eat it *ad libitum*, cautiously, or not at all. The Key Eats Code database was created based on nutritional information gathered from the United States Department of agriculture food database to categorize foods based on the amount of net carbohydrates. Foods labeled as green indicate participants can eat as much as they want; they are very low in carbohydrates and higher in fats. Foods labeled red should be avoided; these are typically high-carbohydrate and high sugar foods like pasta, potatoes, or candy. A yellow label means *think before you eat*. These foods can be eaten occasionally in moderation. There is a *Heart First* badge to indicate foods that are rich in monounsaturated and omega-3 polyunsaturated fats and low in saturated fats. Participants in this trial will be encouraged to eat foods with this badge. There is additionally a *Power Food* badge indicating a food that is especially high in healthy fats and promotes ketosis. For the trial, participants are told to aim to prioritize foods that fall in the green and heart-first category. While conventional ketogenic diets prioritize increased fat intake regardless of source, Keyto emphasizes plant and fish-based fats that are generally lower in saturated fatty acids and higher in unsaturated fatty acids. Research has shown that substituting saturated fats with unsaturated fats can improve cardiovascular disease risk markers [24,25].

Participants will be asked to measure their breath acetone concentrations with the Keyto sensor 3 times daily (immediately after waking up in the morning, before lunch, and before dinner). For this, the participants will be asked to exhale into the hand-held device, which is paired with the participant’s phone. Participants will be able to drink alcohol in moderation but will be instructed to avoid blowing into the Keyto sensor after having an alcoholic beverage.

